### Evaluation

#### Design

We will employ a two-group pre-post quasi-experimental design to conduct a mixed methods evaluation of the I-TREC program in Punjab, India. While the I-TREC program is implemented within the health system by clinicians, we will assess indicators at the levels of facilities, clinicians, patients, and communities.

#### Ethics

The evaluation protocol was reviewed and approved by the ethics committee at All India Institute of Medical Sciences (AIIMS), New Delhi, India (IEC-361/07.07.2017). Given that the Government of Punjab will be implementing I-TREC, and role of research partners is limited to program design, training, and evaluation, this study was deemed to be observational. The role of researchers at Emory University, Atlanta was deemed Not Human Subjects Research (IRB00098808). Participants from whom our research team collects data for evaluation purposes will provide written informed consent following procedures approved by the AIIMS Ethics Committee.

#### Outcomes

Program indicators are guided by the Reach, Effectiveness, Adoption Implementation, and Maintenance (RE-AIM) framework [31]. The principal endpoints for evaluation are shown in Table 2, and focus on the domains of reach, effectiveness, adoption, and implementation of the program components. Reach and effectiveness will be assessed using a combination of community-based data and facility-based data. For example, the proportion of adults ages 30 and older in the community who are screened for hypertension is a measure of reach that will be obtained through a representative community survey. A second measure of reach is the number of patients seeking care for hypertension and diabetes who have an eCRF, which will be measured through health facility data. Similarly, effectiveness will be assessed through health outcomes (e.g., reductions in mean blood pressure and/or mean blood glucose) among patients attending program facilities and also among adults with hypertension and/or diabetes in the community. Adoption metrics focus on healthcare provider utilization of the eCRF and CDSS tools. Implementation measures focus on quantifying the proportion of patients who receive care through the eCRF and CDSS tools. Finally, maintenance will be assessed through qualitative research with stakeholders within the health system to understand views of sustainability.

**Table 2 Tab2:** Key outcome indicators for the I-TREC evaluation

RE-AIM domain	Key indicators
**Reach**	Proportion of adults ages 30 and older in the community screened for hypertension by a government healthcare provider
	Proportion of adults ages 30 and older in the community screened for diabetes by a government healthcare provider
	Number of patients seeking care for hypertension and diabetes at a government health facility who have an eCRF
**Effectiveness**	Reduction in mean blood pressure in patients receiving care in program facilities
	Reduction in mean blood glucose in patients receiving care in program facilities
	Proportion who achieve blood pressure and blood glucose control among patients receiving care in program facilities
	Proportion who achieve blood glucose control among patients receiving care in program facilities
	Reduction in mean blood pressure in the community
	Reduction in mean blood glucose in the community
	Proportion of hypertension patients who achieve blood pressure control in the community
	Proportion of diabetes patients who achieve blood glucose control in the community
**Adoption**	Proportion of healthcare providers (by type) who log into the NCD portal
	Proportion of clinicians who fully or partially accept CDSS prompts
	Proportion of healthcare providers (by type) who report satisfaction with the eCRF+CDSS
**Implementation**	Percentage of hypertension patients who received guideline-based care through the eCRF+CDSS (of all registered patients with hypertension)
	Percentage of diabetes patients who received guideline-based care through the eCRF+CDSS (of all registered patients with diabetes)
	Percentage of hypertension patients who made repeat visits to health facility
	Percentage of diabetes patients who made repeat visits to health facility
	Percentage of “up-referral” cases who attend appointments
	Percentage of patients who were seen at a higher level facility that returned to the Sub-Centre for ongoing management (“closing the referral loop” and ensuring continuity of care)
	Percentage of patients tracked with multiple visits over the course of the program
	Mean time for data upload from each level of facility to central server
**Maintenance**	Views of program sustainability and barriers to sustaining and disseminating the program (qualitative)

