The community survey sample size was determined to estimate differences in mean reduction in systolic blood pressure among those with diagnosed hypertension in the community. First, we computed the base sample size required to detect a desired effect size of 5 mmHg given the SBP standard deviation of 18.5, power = .80 and α = .05, based on the mPower Heart Study [24]. We estimated that 168 individuals with hypertension would be needed to detect the anticipated effect size. Second, we estimated that we would require a sample size of 839 adults in the general population to identify 168 individuals with hypertension, assuming prevalence of diagnosed hypertension of 20%. Third, we determined the optimal sample allocation for a multi-stage sampling design that would be time-efficient for field work and statistical precision. We assumed an intraclass correlation of systolic blood pressure of 0.018 based on village-level clustering of SBP in the DISHA study [32] (unpublished findings). After applying a 10% refusal rate based on our prior field studies in the region, we determined that a cluster size of 50 adults per village distributed across 35 villages per block was optimal. This yielded a total sample size of 3508 for the community survey to be evenly split between the program and comparison blocks.

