#### Health outcomes among patients receiving the I-TREC program

Using patient health data from the eCRF, we will assess processes of care and changes in blood pressure and blood glucose outcomes over time among patients with hypertension or diabetes who seek care at I-TREC program facilities in a facility-based evaluation component. Because I-TREC is being integrated into the routine care in the program block under real-world conditions, we will not be assigning individual patients to treatment nor actively following patients for research visits. Rather, all adults residing in the I-TREC catchment area (i.e., residents of Mukandpur block) will be exposed to the program and patient data will be collected every time a person chooses to receive care at a government health facility. Data from all patients visiting facilities in the program block captured in the Government of India eCRF will be de-identified and obtained by AIIMS throughout the program period for monitoring and evaluation purposes.

The sample size for the facility-based evaluation is out of our control and contingent on the number of patients who seek care at government facilities. We therefore report the detectable effect size for longitudinal change in systolic blood pressure over time in patients at I-TREC facilities after setting power to 80% and α = .05. The program block, Mukandpur, has a population of 98,000. We expect that 30% of the local population will seek care at a government facility, 50% will be age-eligible (30 years and older) per the government guidelines for universal and opportunistic screening of hypertension and diabetes, and 20% will test positive for hypertension, amounting to an estimated patient pool of 2940 adults. Assuming that 50% of all enrolled patients with hypertension and diabetes make repeat visits (enabling us examine changes in outcomes), we will be able to detect a 1.35 mmHg difference in SBP.

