#### Statistical analysis plan

Quantitative data analysis will be performed using SAS, STATA, and R software. Descriptive analyses of the community-based data will examine socio-demographic characteristics, health indicators, and healthcare behaviors of the program and comparison block samples at baseline and end-line. The quantitative evaluation of health and healthcare endpoints will focus on assessing changes in the continuum of care indicators and mean blood pressure in the community-based surveys. We will assess changes in baseline to end-line indicators of health outcomes (e.g., blood pressure) and changes in continuum of care indicators (e.g., proportion screened) for both the program and comparison blocks; see Table 2 for indicators. A simple difference-in-difference (DiD) [33] estimate for each indicator will be computed as
$$ \mathrm{DiD}=\left({p}_{g=\mathrm{i},\mathrm{t}=1}-{p}_{g=\mathrm{i},\mathrm{t}=0}\right)-\left({p}_{g=\mathrm{c},\mathrm{t}=1}-{p}_{g=\mathrm{c},\mathrm{t}=0}\right) $$where p indicates prevalence or mean of each indicator; *g* subscripts group (i = program; c = comparison); and t subscripts the time point of data (0 = pre-program; 1 = post-program). We will estimate log-binomial models (binary outcomes) or linear models (continuous outcomes, with log-transformation if needed) with robust variance to compute the DiD after accounting for compositional characteristics of the community and clustering of data within villages. For each outcome indicator separately, the following model will be estimated using individual-level data:
$$ \mathrm{Outcome}\ \mathrm{indicator}\sim \mathrm{program}\ \mathrm{group}+\mathrm{pre}-\mathrm{post}\ \mathrm{indicator}+\mathrm{program}\ \mathrm{group}\ \mathrm{x}\ \mathrm{pre}-\mathrm{post}\ \mathrm{indicator}+\mathrm{age}+\mathrm{sex}+\mathrm{education}+\mathrm{religion}+\mathrm{marital}\ \mathrm{status}+\mathrm{below}\ \mathrm{poverty}\ \mathrm{line}+\mathrm{facility}\ \mathrm{type}\ \left(\mathrm{public}\ \mathrm{versus}\ \mathrm{private}\right). $$

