The coefficient associated with the interaction term, “program group x pre-post indicator,” is the adjusted DiD estimate accounting for heterogeneity in socio-demographic characteristics. The model will be estimated using generalized estimating equations (GEE) to account for clustering of outcomes within the villages (i.e. village is the cluster variable specified for statistical analysis). Sub-group analyses will examine differences by gender and socioeconomic status.

Data points recorded in the I-TREC system will be analyzed by month to examine trends over time and seasonality. We will also evaluate change patient outcomes over time (e.g., mean SBP change). While several of the I-TREC platform indicators are purely descriptive measures of performance (e.g., mean time for data upload), other indicators of healthcare delivery may be compared between I-TREC facilities and comparison group facilities (e.g., patient volume).

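### All 22 quantitative Table 2 indicators are called principal and none is designated primary, although the survey is sized on one quantity that is not a Table 2 row

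*Protocol article*

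**What the plan says.** - **Status of the endpoints.** The Outcomes section says: "The principal endpoints for evaluation are shown in Table 2, and focus on the domains of reach, effectiveness, adoption, and implementation of the program components". By count, Table 2 has 3 Reach, 8 Effectiveness, 3 Adoption and 8 Implementation rows, which makes 22 quantitative indicators, plus one qualitative Maintenance row. None is ranked. Four Effectiveness rows concern patients in program facilities and four concern the community.
- **Analysis.** In the Statistical analysis plan section a DiD "estimate for each indicator will be computed as" a four-cell contrast, and then "For each outcome indicator separately, the following model will be estimated using individual-level data". The stated focus is plural: the quantitative evaluation "will focus on assessing changes in the continuum of care indicators and mean blood pressure in the community-based surveys". Subgroups follow without a label: "Sub-group analyses will examine differences by gender and socioeconomic status".
- **Sizing of the survey.** "The community survey sample size was determined to estimate differences in mean reduction in systolic blood pressure among those with diagnosed hypertension in the community". The inputs are 5 mmHg, SD 18.5, power .80 and alpha .05.
- **Sizing of the facility component.** With about half of an estimated 2940 patients returning, "we will be able to detect a 1.35 mmHg difference in SBP". The Summary concedes that the comparison block has no data source comparable to the eCRF.

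**The concern.** An evaluation that sizes its survey on one quantity normally lets that quantity decide. Here the quantity has no row of its own. The nearest row, mean blood pressure in the community, names neither systolic pressure nor diagnosed hypertension. Every other row, including the uncontrolled facility changes, has the same formal standing.

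A null community DiD alongside a small fall in facility blood pressure, or one significant control proportion alongside a null systolic result, would each be a result on a principal endpoint. Nothing in the endpoint or analysis text settles which prevails, so the conclusion could rest on a choice made after the data are seen.

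**Working it through.** **1. Reproduce the article's sizing figures.**

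Community survey, two-group comparison of means, n per arm = 2 × [SD × (z_alpha + z_power) / difference]²:
- one-sided .05: 2 × [18.5 × (1.645 + 0.842) / 5]² = 169.3, close to the stated 168;
- two-sided .05: 2 × [18.5 × (1.960 + 0.842) / 5]² = 214.9, which does not match. With 168 per arm, two-sided power is about 0.70.

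The rest of the chain holds: 168 / 0.20 = 840 (stated 839); design effect 1 + 49 × 0.018 = 1.882; 839 × 1.882 / 0.9 = 1754 per block; doubled and unrounded, 3508.9 (stated 3508).

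Facility component: 98,000 × 0.30 × 0.50 × 0.20 = 2940; half is 1470; 18.5 × (1.960 + 0.842) / √1470 = 1.35 mmHg, as stated. This one matches a two-sided, single-group calculation.

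**2. Is the sized quantity the planned contrast?**

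A DiD from four independent cross-sections has twice the variance of a two-group difference with the same n per cell. The n per cell is 4 × [18.5 × (z_alpha + 0.842) / 5]², which gives about 339 one-sided or 430 two-sided before any design effect. The base of 168 matches neither.

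**3. Which rows can receive a DiD?**

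The community-survey rows clearly can: 2 screening (Reach), 2 mean-level and 2 control (both Effectiveness). That is 6 of 22, of which 4 are Effectiveness. The facility Effectiveness rows have no comparable comparison-block data, and the tool-use rows concern tools that exist only in the program block.

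**4. How easily could an uncontrolled facility row look positive?**

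Using the inputs that reproduce 1.35, the standard error is 18.5 / √1470 = 0.483 mmHg. An observed mean fall of 1.96 × 0.483 = 0.95 mmHg would reach two-sided .05 whatever its cause.

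**5. Chance of at least one nominally significant DiD when nothing works.**

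Assumptions, none stated in the article: each DiD is tested at .05 two-sided, any one significant result counts, and the test statistics share a common correlation. Independent case: 1 − 0.95^k. Correlated cases: simulation with 1,000,000 multivariate-normal draws.

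| DiDs counted | independent | correlation 0.5 | correlation 0.9 |
|---|---|---|---|
| 4 community Effectiveness | 0.186 | 0.156 | 0.094 |
| 6, adding the 2 screening rows | 0.265 | 0.208 | 0.109 |

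Divided by .05, the four-row case is 3.7, 3.1 and 1.9 times. Counting only favourable-direction results for those four rows gives 0.096, 0.078 and 0.047, against .025 for a single test. With one-sided .05 tests, the level at which the base n reproduces, it gives 0.186, 0.145 and 0.087.

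**The case against.** The strongest reply is that this is a journal article condensing a fuller protocol, so endpoint hierarchy and multiplicity rules may sit in a document not shown. A RE-AIM evaluation also reports several domains by design. That reply disposes of any complaint about a missing alpha split or adjustment method. It does not dispose of what the article does say: it gives every Table 2 row principal status while sizing the survey on a quantity outside the table.

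A second reply is that the article has an implicit order. The analysis focuses on the community surveys, the survey is sized on systolic pressure, some platform indicators are called purely descriptive, and the Summary presents the community survey as partly offsetting the lack of comparison-block patient data. This stands in part. The contrast itself is defined (the group-by-period interaction), and the intended weight is visible. But the stated focus still spans several indicators, and no row is given precedence.

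A reader might also infer that all of Table 2 is tested at .05, and that a false effectiveness claim is therefore about four times as likely as the article states. The document does not support this. The value .05 appears only in the two sizing calculations, no familywise rate is stated to be exceeded, and a DiD is clearly available for only six rows, two of which are Reach. Adding the four facility rows to the count would be unsound: their main problem is bias from having no comparator, which a familywise rate does not measure.

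**Conclusion.** The point holds as a defect in the endpoint structure: an unranked principal label over 22 quantitative rows, a survey sized on a quantity that is not one of them, and uncontrolled facility changes given the same standing as the controlled DiD.

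Its size depends on how the results would be used, which the article does not say. If any one nominally significant community Effectiveness DiD were taken as proof, the error chance would be roughly 2 to 4 times that of a single .05 test: 0.09 at correlation 0.9, up to 0.19 if independent. The correlations, the two-sided level and the any-one rule are all assumptions. The range shows what is at stake if no primary is named; it is not an error rate that the plan commits to.

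**What to change.** In the Outcomes and Statistical analysis plan sections, before endline data are analysed:

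- Name one primary indicator with its measure and population: the program-by-period DiD in mean systolic blood pressure among community-survey adults with diagnosed hypertension, the population used for sizing. State whether the test is one- or two-sided.
- Label the other community indicators secondary. Either test them by Holm or in a fixed order, or report estimates with 95% confidence intervals and no confirmatory claim.
- Label the facility Effectiveness rows and the process rows descriptive, and the gender and socioeconomic subgroups exploratory.
- State that uncontrolled facility changes cannot override the community DiD.
- Do not describe the primary DiD as powered at 80% for 5 mmHg. The base of 168 matches a one-sided two-group comparison, so report what the achieved sample can detect for the four-cell contrast.

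The cost is wording only, with no new data or participants. The downside is that a significant secondary, facility or subgroup result could no longer support a stand-alone claim of effectiveness.

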## Methods/discussion

### Setting and target population

I-TREC was developed as a collaboration between the All India Institute of Medical Sciences, New Delhi (AIIMS), the Centre for Chronic Disease Control (CCDC), and Emory University. For over a decade, these three institutions have collaboratively developed and tested the combination of information technology (IT), enhanced personnel training, and workflow alterations to improve the quality of care for diabetes and hypertension in diverse settings across India [22–29]. Most of these prior efforts focused on a single level of the healthcare system and relied on research staff to implement the intervention. In I-TREC, however, our goal was to develop and evaluate a coordinated package of tested tools and provider training approaches that catered to functions and personnel available in each type of the 4-tier healthcare system (see Table 1). We further sought to embed the program within the infrastructural scaffolding provided by the Government of India in the interest of future scalability. I-TREC was thus designed to be implemented by personnel and using resources (medications, diagnostics) already present within the public healthcare system.

**Table 1 Tab1:** Intervention components

Healthcare facility level	I-TREC components	Available Staff	Tasks and functions
**Level 1: Village Sub-Centre**	eCRF	ANM	Universal screening of hypertension and diabetes for adults ages ≥ 30 y in the community Enrol community members into the NCD portal Adults with blood pressure ≥ 140/90 or random blood glucose ≥140 mg/dl referred to medical officer at nearest facility (level 2) for confirmation and initiation of treatment
**Level 2: Primary Health Centre**	eCRF+CDSS	SN, MO	Confirmatory diagnosis of hypertension and diabetes of suspected cases referred from sub-centre Routine management of adults with stable hypertension and diabetes Generate and update eCRF Use CDSS to develop treatment plan and determine need for up-referral
**Level 3: Community Health Centre**	eCRF+CDSS	SN, MO	Run dedicated NCD clinics Routine management of adults with stable hypertension and diabetes Generate and update eCRF Use CDSS to develop treatment plan and determine need for up- or down-referral

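### The facility blood pressure and glucose Effectiveness endpoints are uncontrolled changes in returning patients, partly selected on raised readings, so a fall beyond 1.35 mmHg would not by itself show a program effect

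*Protocol article*

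**What the plan says.** The Outcomes section calls the Table 2 indicators the principal endpoints. Under Effectiveness they include "Reduction in mean blood pressure in patients receiving care in program facilities", the same for glucose, and control proportions in program-facility patients. The community versions are listed separately.

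The section on health outcomes among patients receiving the program draws the facility data from the program-block eCRF. It builds the expected cohort as follows: "The program block, Mukandpur, has a population of 98,000"; "We expect that 30% of the local population will seek care at a government facility"; half are age-eligible; a fifth test positive for hypertension. This gives 2940 adults. It continues "Assuming that 50% of all enrolled patients with hypertension and diabetes make repeat visits" and concludes that "we will be able to detect a 1.35 mmHg difference in SBP", "after setting power to 80% and α = .05".

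On entry to care, Table 1 has at Sub-Centre level: "Adults with blood pressure ≥ 140/90 or random blood glucose ≥140 mg/dl referred to medical officer at nearest facility". A confirmatory diagnosis at the Primary Health Centre follows. Screening at health facilities is also opportunistic.

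The Statistical analysis plan section describes the difference-in-difference model for the community surveys, with village as the cluster. For eCRF data it mentions monthly trends and change in patient outcomes over time. The Summary states that the comparison block has no comparable patient data and that the community survey is meant in part to mitigate this. Regression to the mean and selection of returning patients are not mentioned.

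**The concern.** Three features coincide in one endpoint: no comparator, entry partly through a high reading, and follow-up only in those who come back. A group chosen because a reading was high will on average read lower next time, whether or not care has changed. Patients who return may also differ from those who do not. The article reports that COVID-19 reduced patient flow and closed facilities intermittently, so who returned may have shifted during follow-up. Refresher content training is given in both blocks, so even a real fall in program facilities could not be credited to the eCRF and CDSS from these data alone.

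The survey draws separate cross-sections before and after. It gives a controlled community estimate, but it cannot correct a within-patient facility change. What is at stake is the reading of the results: a significant facility fall could be reported as effectiveness beside a null survey difference-in-difference.

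**Working it through.** **1. Reproduce the stated figure.** Inputs from the facility section: 98,000 × 0.30 × 0.50 × 0.20 = 2940, and 2940 × 0.50 = 1470 returning patients. That section gives no SD, so the survey calculation's SD is used ("given the SBP standard deviation of 18.5"). Two-sided testing is assumed.

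Detectable mean change = (1.960 + 0.842) × SD / √n = 2.802 × 18.5 / √1470 = **1.352 mmHg**.

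Alternatives do not match: one-sided 1.20; two independent groups of 1470 each, 1.91; two groups of 735, 2.70; the full pool of 2940, 0.96. So 1.35 is a one-sample change without a design effect.

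**2. What that SD implies.** SD of change = SD × √(2(1 − r)), where r is the between-visit correlation. This equals 18.5 when r = 0.5.

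**3. Regression to the mean with no treatment effect.** Assumptions: normal SBP, population SD 18.5, selection on SBP alone in the upper 20% (the plan's share testing positive). The article gives neither r nor the baseline reading, so both are varied.

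(a) Baseline is the qualifying reading: (1 − r) × 18.5 × φ(0.842)/0.20 = (1 − r) × 25.9.

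(b) Baseline is a confirmatory reading that must also exceed the cut: simulated, 4 million draws.

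(c) Baseline is a later reading not used for selection: about 0 at every r.

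| r | (a) mmHg | (b) mmHg |
|---|---|---|
| 0.5 | 12.9 | 9.3 |
| 0.6 | 10.4 | 7.1 |
| 0.7 | 7.8 | 5.0 |
| 0.8 | 5.2 | 3.1 |
| 0.9 | 2.6 | 1.5 |

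Under (a), the value falls to 1.35 only at r of about 0.95 (1 − 1.35/25.9).

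**4. Dilution by known patients.** If previously known patients contribute no regression to the mean, the newly selected share at which the cohort mean reaches 1.35 is 1.35 divided by the table value. Under (a) this is 10% at r = 0.5, 17% at 0.7, 26% at 0.8 and 52% at 0.9. Under (b) it is 1.35/9.3 = 14% at r = 0.5, 1.35/5.0 = 27% at 0.7, 1.35/3.1 = 43% at 0.8, and about 93% at 0.9 (1.35/1.454, unrounded).

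**5. Clustering, as a range.** The only ICC given is 0.018, for village-level SBP in the survey calculation. The article counts 21 program-block facilities. If 1470 patients are spread equally, that is 70 each: design effect 1 + 69 × 0.018 = 2.242, and 1.352 × √2.242 = 2.02 mmHg. With an assumed 10 facilities (147 each): 1 + 146 × 0.018 = 3.628, and 1.352 × √3.628 = 2.6 mmHg. With 21 facilities but r = 0.8, the SD of change is 18.5 × √0.4 = 11.7, the unclustered figure is 0.855, and the clustered one 0.855 × √2.242 = 1.28 mmHg.

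No SD or correlation is given for glucose. The same argument applies there in direction, but it cannot be sized.

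**The case against.** The strongest reply is that the article largely handles this already. It discloses the missing comparator, centres its quantitative health evaluation on the surveys with difference-in-difference, and gives the eCRF data only trends and change over time. Effectiveness is a RE-AIM domain name, 1.35 mmHg is a detectable difference and not a claimed effect, and the reliance on repeat visitors is stated. This is fair as far as it goes. However, the disclosure covers the comparator and not the two selection effects, and the facility changes remain among the principal endpoints.

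The reply also stands on case mix. Screening results at Sub-Centres go into a separate portal; the eCRF is generated at Primary Health Centres and above, after or alongside confirmation. The screening reading is therefore not shown to be the eCRF baseline. The cohort includes patients under routine management and patients with diabetes who were not selected on blood pressure. Opportunistic facility screening still leaves some selection on an eCRF reading.

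A reader might infer that 1.35 mmHg is wrong and should be 2.0. The documents do not support that. The figure reproduces exactly; the ICC is for villages and for SBP level, not for facilities and within-patient change; and some of the 21 facilities are probably Sub-Centres, below the level where the eCRF is generated.

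Baseline definitions and model details can properly sit in an unseen SAP, so their absence here is not the fault. The fault is the label and role given to an uncontrolled change.

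**Conclusion.** The point holds conditionally. The facility blood pressure and glucose changes are uncontrolled, come from a cohort partly identified through raised readings, and are observable only in those who return. If a qualifying or confirmatory high reading is the baseline, regression to the mean in newly detected patients is about 1.5 to 13 mmHg for r from 0.9 to 0.5. That ranges from just above the stated 1.35 mmHg to more than nine times it. It is smaller with known patients mixed in, and near zero with a baseline not used for selection. All of this rests on normal SBP, a population SD of 18.5 and selection of the upper fifth.

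A reader might infer that regression to the mean certainly far exceeds 1.35 mmHg, or that a significant fall is nearly guaranteed without any effect. The documents do not support either, because correlation, baseline reading and case mix are not given. What is supported is narrower: a significant fall on these endpoints would not show program effectiveness. The 1.35 mmHg is arithmetically correct as the precision of an uncontrolled mean change, given an SD of change of 18.5 and no facility clustering.

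**What to change.** - Report facility blood pressure and glucose change as descriptive, and base effectiveness conclusions on the two-block survey difference-in-difference.
- Take as baseline the first eCRF reading after the qualifying visit, or report newly detected and previously known patients separately.
- Compare the characteristics and first readings of returners and non-returners.
- Analyse all available readings in a model that allows for facility clustering.
- State that 1.35 mmHg is the precision of an uncontrolled mean change with SD of change 18.5 and no clustering. Add a range instead of one replacement figure: for example about 2.0 mmHg under ICC 0.018 and 21 equal facilities, lower if the SD of change is smaller.

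This changes wording and analysis only; no new data are collected. The cost is somewhat lower precision. A patient with only a qualifying reading adds no change information and, under the later baseline, one with a single later reading has a baseline but no change. Visits per patient are not given, so the loss cannot be computed. If treatment starts at the qualifying visit, the later baseline also misses part of any early fall; separate reporting of new and known patients avoids that but leaves regression to the mean in the new group.
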